#### National fibromyalgia and chronic fatigue patient association

Initially, a letter containing information about the trial, what participation involves and the written informed consent form is sent to all members of the association from the Lisbon and Porto region that meet the inclusion/exclusion criteria and have previously indicated they were available for participation in research studies. Patients who wish to participate in the study return the written informed consent and are subsequently randomly assigned to either the intervention or the control group.

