#### Intervention group

In addition to standard care, patients in the intervention group receive the 4-STEPS program that consists of:

1. Two face-to-face individual motivational interviewing (MI) sessions aimed at exploring important health and life goals, increasing participants' motivation and confidence to be physically active and setting a specific personal physical activity goal. The first MI session takes place 1 week after the baseline assessment and the second MI session takes place 2 weeks after the first. The MI session is delivered by a psychologist with MI training (member of the research team). The duration of the sessions is approximately 1 hour. Details on the topics addressed in the MI sessions are presented in Table 1.

2. Two brief telephone counseling sessions: These sessions take about 20 minutes and are provided 2 weeks and 6 weeks after the last MI session. Details on the topics addressed during the telephone sessions are presented in Table 1.

**Table 1 T1:** 4-STEPS sessions content

4-STEPS sessions	Topics
**Motivational Interviewing- Session 1**	✓ Listen to patient complaints, with emphasis on fatigue.
	✓ Illness perceptions.
	✓ Exploration of patients' present physical activity behavior.
	✓ Current health behaviors and other activities are explored (physical activity, sleep, pain, etc.).
	✓ Discussion of the information on the booklet given previously (specially the relation between CF major symptoms and physical activity behavior and boom-bust pattern).
	✓ Motivation and Confidence Scales: Exploration of the willingness to engage in physical activity (or adjust current physical activity behavior) and the confidence in one's own capability to achieve this behavior with success.
	✓ Discussion of the pros and cons (not-) to change physical activity behavior (Decisional Balance).
	✓ Social support network is addressed.

**Motivational Interviewing- Session 2**	✓ Exploration of possible competing goals with physical activity (e.g. housework chores) and link to core values.
	✓ Strategies to overcome obstacles to physical activity and competing goals are addressed.
	✓ Based on the register of daily activities and steps taken (pedometer register) and GET scheme for physical activity, the patient establishes a personal physical activity goal for the following two months.

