	✓ Discuss the possible reasons for perpetuation of symptoms and difficulty to change health behaviors in CF patients, namely perfectionism, fear of movement, presence of stressful situations and boom-bust pattern. (some are already mentioned at the first motivational interview and are now emphasized).
	✓ Exploration of emotion control importance and techniques (e.g. relaxation techniques).

**Telephone sessions:**	✓ Revision of the physical activity goal planning (adequacy to the patients' present situation).
	✓ Relapse prevention (strategies to overcome new or persisting difficulties to physical activity and emotion control strategies).

3. Self-regulation (SR) booklets: There are two booklets that are designed to help patients change their level of physical activity (Informational booklet and Workbook). The Informational booklet is provided at the end of the baseline assessment, the "Step 1" part of the Workbook is provided at the first MI session and the parts "Step 2", "Step 3" and "Step 4" are given during the second MI session. Details on the topics that are addressed in the SR booklets are presented in Table 2.

4. A pedometer to register physical activity on a daily basis (steps taken) during the 3 month intervention period. Instructions on how to use the pedometer are given in the baseline assessment session (Table 2).

5. Daily activities record (Table 2): Patients receive several daily activity records (physical activities, mental activities and rest). The first daily activity record is given to the patient at the end of the first MI session; patients are asked to fill out the activity record in the time period between the first and second MI session. This homework assignment aims at evaluating the patients' daily activities management and possibly recognizing an erratic pattern of rest and activity (boom and bust cycle). At the end of the second MI session, patients receive daily activities records that can be used to monitor changes in daily activity patterns during the subsequent nine weeks.

6. Leaflet for family (Table 2): At the end of the first MI session patients receive a leaflet for their partner or significant other in order to increase social support.

**Table 2 T2:** 4-STEPS Materials content

4-STEPS materials	TOPICS

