### Assessments

Measures will be collected at baseline, 3 months later and 12 months after baseline. All measures are self-report. Data will be collected in both the health care institutions and the patient association, at all times (Table 3). Primary and secondary outcomes, predictors and process evaluation measures are described below. A description of measures and time points can be found in Table 3.

**Table 3 T3:** Measures to be administered at each time point

	Baseline	Post-test	12 months
Demographics	X		
Severe infection	X		
Life event	X		
Medical advice	X		
Duration Symptoms and diagnosis	X		
CFS symptom checklist	X	X	X
Presence of FM symptoms	X	X	X
CIS-20R	X	X	X
Impact of fatigue	X	X	X
NFR	X	X	X
Work related questions	X	X	X
Brief IPQ-R	X	X	X
Brief IPQ-R causes subscale	X		
CERQ positive subscales	X	X	X
PCS	X	X	X
BRIQ	X	X	X
Social support	X	X	X
BSI	X	X	X
Sleep	X	X	X
PHQ-15	X	X	X
SF-12	X	X	X
Physical Activity history	X	X	X
Steps taken (pedometer)	X	X	X
Physical activity intention	X		
Action planning	X		
Coping planning	X		
SRSB Physical activity goal elicitation	X		
SRSB Physical activity goal progress	X	X	X
SRSB goal efficacy scale	X		
SRSB all scales		X	X
Barriers Efficacy	X	X	X
TSRQ	X	X	X
Intervention evaluation (intervention condition)		X	

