#### Secondary outcomes

1. Fatigue severity, assessed by means of the CIR-20R [35].

2. ICF and CFS diagnosis will be assessed by means of the CDC criteria and using the CDC-CFS Symptom Inventory [36].

3. Presence of Fibromyalgia symptoms.

4. Fatigue impact is assessed by means of a modified version of the pain interference subscale of the Brief Pain Inventory (BPI) [37].

5. Work or daily activities related fatigue is assessed by means of the Need for Recovery Scale (NFR) [38].

6. Use of health care resources is measured on the basis of two questions: (1) number of visits to the primary care physician and medical specialists, (2) use of medication.

7. Work related information: currently (not) working, if currently working, number of hours working, working part-time due to fatigue, dropped out of work due to fatigue, number of days absent from work.

8. The All-or-nothing and Limiting behaviour scales from The Behaviour Responses to Illness Questionnaire (BRIQ) [39] are used to assed behavioural symptom management.

9. Anxiety and depression are measured with the Brief Symptom Inventory (BSI) [40,41].

10. Quality of sleep is assessed with five questions based on the DSM-IV criteria for sleep disorders [42] and six questions from the Pittsburgh Sleep Quality Index (PSQI) [43].

11. Number and severity of physical symptoms is measured by means of the Patient Health Questionnaire-15 (PHQ-15) [44].

12. Physical and emotional functioning is measured with the Short Form Health Survey-12 (SF-12 V.2) [45].

13. Physical activity: two different measures are used to assess physical activity level. The first is the pedometer (YAMAX SW-200), a portable device that counts the number of steps taken, by detecting hip motions. Participants are asked to use the pedometer on a daily basis for seven consecutive days and register their daily number of steps on a form that is provided to the patient. The second measure is the Sports subscale of the SQUASH [46]; in this subscale participants indicate the type of physical activity they do (e.g. swimming) including the frequency per week (e.g. 3 days per week) and duration per day (e.g. 50 minutes) for each of these activities. The intensity of each of these activities is calculated based on the Ainsworth's Compendium of Physical activities [47].

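### The protocol does not place the 7-day baseline step count before allocation and booklet delivery, so baseline steps in the intervention arm may already carry part of the booklet's effect

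*Protocol article*

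**What the plan says.** All references are to the protocol article.

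- **Enrolment.** Under Health care institutions, assignment to an arm is the last step listed. Under the patient association heading: "Patients who wish to participate in the study return the written informed consent and are subsequently randomly assigned". Neither section mentions a baseline assessment before assignment.
- **Booklet.** Intervention group, item 3: "The Informational booklet is provided at the end of the baseline assessment". The item presents the booklets as tools for changing activity level. Table 2 lists the content: activity guidelines, benefits of activity in chronic fatigue, suitable activities such as walking, and the boom-bust pattern.
- **Pedometer.** Intervention group, item 4: "Instructions on how to use the pedometer are given in the baseline assessment session".
- **First MI session.** Intervention group, item 1: "The first MI session takes place 1 week after the baseline assessment". Table 1 has that session include "Discussion of the information on the booklet given previously".
- **Step count.** Secondary outcomes, item 13: "Participants are asked to use the pedometer on a daily basis for seven consecutive days". Table 3 schedules it at baseline, post-test and 12 months.
- **Control arm.** Controls receive a flyer on the health benefits of activity and the activity guidelines. The time of handing it over is not given.
- **Analysis.** The Analysis plan names MAN(C)OVA and AN(C)OVA for the primary and secondary outcomes, without covariates.
- **Objective.** The Background closes by naming two aims: promoting physical activity and reducing fatigue.

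**The concern.** A baseline value can safely serve as a covariate, or be subtracted from follow-up, only if the randomised treatment cannot have affected it. Here an arm-specific item meant to raise activity appears to be in patients' hands during the week in which baseline activity is counted. If so, baseline steps are measured after randomisation. Adjusting for them or subtracting them then removes part of the effect that the trial sets out to estimate.

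At stake is the step count. It is a secondary outcome and one of two physical activity measures (the other is the SQUASH sports subscale), but promoting activity is one of the two parts of the main objective.

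**Working it through.** **Step 1: order of events.** The protocol gives no date for the baseline step week, so the order has to be inferred.

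1. An arm-specific booklet is handed over when the baseline assessment ends, so allocation is known by then at the latest.
2. Pedometer instructions belong to the baseline session. A patient first instructed there can start a seven-day count only from that session on.
3. The first MI session is one week after baseline, which is exactly the length of the count.
4. According to Table 2 and item 3, the Workbook part handed over at the first MI session starts a two-week pedometer log between the two MI sessions. Table 2 also treats the intervention's pedometer record as separate from the one used for assessment. Intervention logging therefore seems to begin at the first MI session, which leaves the week before it as the natural place for the baseline count.
5. The booklet is discussed at the first MI session as something already received, so it is in the patient's hands at some point before that session.

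The most natural sequence is therefore: assignment, baseline session with booklet, seven-day count, first MI session. The other possible sequence puts the booklet after the count. That would need a contact between the baseline session and the first MI session, and none is described.

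**Step 2: effect on the estimate.** The protocol states no step-count effect, standard deviation or baseline-to-follow-up slope, so there is no figure of its own to reproduce. Let

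- τ = true difference between arms in follow-up steps,
- f = share of τ already present as a between-arm difference in the baseline week, net of any effect of the control flyer (assumed 0.10 to 0.50),
- b = within-arm slope of follow-up on baseline steps (assumed 0.3 to 0.7).

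The expected baseline difference is fτ. Then

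- ANCOVA estimates τ − b·fτ = τ(1 − bf),
- a change score estimates τ − fτ = τ(1 − f),
- a comparison of follow-up values alone estimates τ.

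Share of the true effect retained:

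| f | ANCOVA, b = 0.3 | ANCOVA, b = 0.5 | ANCOVA, b = 0.7 | Change score | Follow-up only |
|---|---|---|---|---|---|
| 0 | 100% | 100% | 100% | 100% | 100% |
| 0.10 | 97% | 95% | 93% | 90% | 100% |
| 0.25 | 92.5% | 87.5% | 82.5% | 75% | 100% |
| 0.50 | 85% | 75% | 65% | 50% | 100% |

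In steps: if the booklet raised the intervention arm's baseline week by a net 500 steps/day (assumed), a change score would understate the effect by 500 steps/day. ANCOVA would understate it by 0.5 × 500 = 250 to 0.7 × 500 = 350 steps/day at slopes of 0.5 to 0.7.

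The row f = 0 applies if the count is in fact finished before the booklet is given.

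**The case against.** The strongest objection is that the order is nowhere stated. Steps are listed as a baseline measure, so the end of the baseline assessment could mean the end of the seven days, and the bias would then be zero. The pedometer sentence in item 4 concerns the device used during the intervention and does not itself date the baseline count. The enrolment sections are short narratives, and Figure 1, which might show the order, is not visible in the text at hand. All of this stands, and it is why the conclusion says may. It does not remove the point, because no statement in the text secures the count before allocation and booklet, and the timings that are given point the other way.

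Three further limits also stand. The control flyer overlaps in content with the booklet and, if given at the same time, would offset part of the contrast. The bias arises only if baseline steps are adjusted for or subtracted, and the protocol does not name its covariates. The size rests entirely on assumed inputs.

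Two stronger readings are tempting but unsupported:

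- A reader might infer that patients could be randomised and then found ineligible at the baseline visit. In both routes the patients approached already meet the inclusion and exclusion criteria. The CDC symptom inventory is listed as a secondary outcome repeated at every time point, not as the entry check.
- A reader might infer that the primary fatigue outcome is biased in the same way. A booklet handed over at the end of the session would follow questionnaires completed in it, and the text does not say when patients learn their arm. The booklet mechanism does not reach fatigue or its sample size.

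**Conclusion.** The point holds as a weakness in how the baseline step count is protected, not as a demonstrated bias. The stated timings suggest that the seven-day count follows allocation and the booklet, and the protocol does not rule this out. If that is the order and the booklet raises steps by more than the flyer does, an ANCOVA or change-score analysis of steps is biased toward no effect. Over the assumed ranges, ANCOVA loses 3% to 35% of the true effect and a change score loses 10% to 50%. The loss is zero if the count comes first. A comparison of follow-up steps alone is not biased by this mechanism. The consequence is confined to a secondary outcome, but one that serves half of the main objective. The trial is described as ongoing, so the order can still be settled for later patients.

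**What to change.** For further patients, state and follow this order: consent, baseline questionnaires and the seven-day step log completed and returned, then disclosure of allocation, then arm-specific material (booklet or flyer).

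For patients enrolled under the present order, add a sensitivity analysis that compares follow-up steps between arms without adjusting for the baseline week. If the count was in fact always completed before allocation was disclosed, a sentence saying so is enough.

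Cost: about one week between consent and allocation, and a later moment for handing over material, with no extra measurement. The trial would contain a mixture of procedures, so the order that applied to each patient should be recorded. The unadjusted sensitivity analysis loses precision. If steps vary equally at baseline and follow-up, so that the slope equals the correlation, its variance is 1/(1 − b²) times that of ANCOVA: 1/0.91 = 1.10 at b = 0.3, 1/0.75 = 1.33 at b = 0.5 and 1/0.51 = 1.96 at b = 0.7. It therefore suits a sensitivity analysis better than a replacement for the adjusted one.

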### Assessments

Measures will be collected at baseline, 3 months later and 12 months after baseline. All measures are self-report. Data will be collected in both the health care institutions and the patient association, at all times (Table 3). Primary and secondary outcomes, predictors and process evaluation measures are described below. A description of measures and time points can be found in Table 3.

**Table 3 T3:** Measures to be administered at each time point

	Baseline	Post-test	12 months
Demographics	X		
Severe infection	X		
Life event	X		
Medical advice	X		
Duration Symptoms and diagnosis	X		
CFS symptom checklist	X	X	X
Presence of FM symptoms	X	X	X
CIS-20R	X	X	X
Impact of fatigue	X	X	X
NFR	X	X	X
Work related questions	X	X	X
Brief IPQ-R	X	X	X
Brief IPQ-R causes subscale	X		
CERQ positive subscales	X	X	X
PCS	X	X	X
BRIQ	X	X	X
Social support	X	X	X
BSI	X	X	X
Sleep	X	X	X
PHQ-15	X	X	X
SF-12	X	X	X
Physical Activity history	X	X	X
Steps taken (pedometer)	X	X	X
Physical activity intention	X		
Action planning	X		
Coping planning	X		
SRSB Physical activity goal elicitation	X		
SRSB Physical activity goal progress	X	X	X
SRSB goal efficacy scale	X		
SRSB all scales		X	X
Barriers Efficacy	X	X	X
TSRQ	X	X	X
Intervention evaluation (intervention condition)		X	

#### Primary outcome

The primary outcome is the reduction of perceived fatigue severity, which is assessed by means of the Checklist of Individual Strength (CIS-20R) [35]. A difference of 7 points between the intervention and the control group on the main dimension (= the subjective feeling of fatigue subscale) of the CIS-20 R is considered to be a clinically significant difference [33,34].

#### Secondary outcomes

1. Fatigue severity, assessed by means of the CIR-20R [35].

2. ICF and CFS diagnosis will be assessed by means of the CDC criteria and using the CDC-CFS Symptom Inventory [36].

3. Presence of Fibromyalgia symptoms.

4. Fatigue impact is assessed by means of a modified version of the pain interference subscale of the Brief Pain Inventory (BPI) [37].

5. Work or daily activities related fatigue is assessed by means of the Need for Recovery Scale (NFR) [38].

6. Use of health care resources is measured on the basis of two questions: (1) number of visits to the primary care physician and medical specialists, (2) use of medication.

7. Work related information: currently (not) working, if currently working, number of hours working, working part-time due to fatigue, dropped out of work due to fatigue, number of days absent from work.

8. The All-or-nothing and Limiting behaviour scales from The Behaviour Responses to Illness Questionnaire (BRIQ) [39] are used to assed behavioural symptom management.

9. Anxiety and depression are measured with the Brief Symptom Inventory (BSI) [40,41].

10. Quality of sleep is assessed with five questions based on the DSM-IV criteria for sleep disorders [42] and six questions from the Pittsburgh Sleep Quality Index (PSQI) [43].

11. Number and severity of physical symptoms is measured by means of the Patient Health Questionnaire-15 (PHQ-15) [44].

12. Physical and emotional functioning is measured with the Short Form Health Survey-12 (SF-12 V.2) [45].

13. Physical activity: two different measures are used to assess physical activity level. The first is the pedometer (YAMAX SW-200), a portable device that counts the number of steps taken, by detecting hip motions. Participants are asked to use the pedometer on a daily basis for seven consecutive days and register their daily number of steps on a form that is provided to the patient. The second measure is the Sports subscale of the SQUASH [46]; in this subscale participants indicate the type of physical activity they do (e.g. swimming) including the frequency per week (e.g. 3 days per week) and duration per day (e.g. 50 minutes) for each of these activities. The intensity of each of these activities is calculated based on the Ainsworth's Compendium of Physical activities [47].

#### Predictors

1. Demographic information (age, gender and education).

2. Presence of a severe infection prior to the onset of fatigue.

3. Duration of fatigue at baseline.

4. Occurrence and current impact (by means of a Visual Analogue Scale from 0 cm- no impact at all to 10 cm-exterme impact) of a serious life event experienced prior to the onset of fatigue.

5. Patients' illness beliefs are assessed by the Brief Illness Perception Questionnaire (Brief IPQ-R) [48].

6. Three subscales of the Cognitive Emotion Regulation Questionnaire - Short Version (CERQ-short) [49] were used to assess adaptive cognitive coping strategies, and a version of the Pain Catastrophizing Scale (PCS) adapted for fatigue [50] was used to measure catastrophic cognitions related to CF symptoms.

7. Level and range of social support are assessed.

8. Goal progress and self-regulation skills to achieve a personal goal are measured with the Self-regulation Skills Battery (SRSB) [51].

9. Self-efficacy to overcome obstacles to physical activity is assessed with the Barriers Efficacy Scale [52].

10. Autonomous and Coerced motivation to be physically active is assessed using the respective scale from the Treatment Self-regulation Questionnaire (TSRQ) [53].

11. Physical activity intention, action planning and coping planning are assessed using the measures from Sniehotta and colleagues [54].

#### Process evaluation

Participant satisfaction with the self-regulation based 4-steps program will be assessed.

### Analysis plan

We will use the SPSS and AMOS software packages for data analysis. Descriptive analysis will be performed for demographics, clinical information and process evaluation, stratified by treatment condition. Differences between the control and intervention group for the primary and secondary outcome measures will be assessed using MAN(C)OVA and AN(C)OVA. We also intend to use regression analysis and structural equation modelling to analyse longitudinal relationships between predictors, possible mediators and outcomes (path analysis).

## Discussion

Physical activity seems to be very important for patients suffering from unexplained chronic fatigue, while SR interventions seem to be effective in promoting long-term health behaviour change. The 4-STEPS program will be the first brief SR based physical activity intervention for ICF/CFS patients. We are not aware of any RCT to promote physical activity in these patients conducted in Portugal. This RCT will provide information on the efficacy of the intervention as well as on the predictors of physical activity, fatigue and other somatic symptoms. The fact that it is a brief intervention, that requires minimal personal contact with the health care professional and that patients receive self-help materials to support them can also be seen as an advantage from a cost-effectiveness point of view if the trial has a significant effect. If proven effective, this program can be considered as an adjunctive treatment for ICF/CFS.

